9.1 Definitions

- *Adverse Event (AE):* Any untoward medical occurrence in a subject to whom a medicinal product is administered and which does not necessarily have a causal relationship with this treatment.

*Adverse Reaction (AR):* In the pre-approval clinical experience with a new medicinal product or new use of a medicinal product, and particularly as the therapeutic dose(s) may not be established, all noxious and unintended reactions to the medicinal product related to any dose should be considered an adverse reaction (AR). The phrase “reaction” to a medicinal product means that the causal relationship between the medical product and an adverse event is at least a reasonable possibility, that is the relationship cannot be ruled out.

*Serious Adverse Event (SAE) Serious Adverse Event (SAE): Any untoward medical occurrence that at any dose requires inpatient hospitalization or prolongation of existing hospitalisation, results in persistent or significant disability or incapacity, results in a congenital anomaly or birth defect, is life-threatening, or results in death.*

*Medical and scientific assessment will be made to determine if an event is serious.*

*Suspected Unexpected Serious Adverse Reactions (SUSAR)*: An adverse reaction/event that is unexpected, serious, and suspected to be caused by the treatment, i.e. adverse reactions/events that are not included in the RSI section of the Investigator’s Brochure (IB) or SmPC.

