4.3 Primary Endpoint

- **Safety:** Incidence of adverse events (AEs) and serious adverse events (SAEs) during the trial period.

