4.4 Secondary Endpoints

- Time to **Relapse:**

Defined as a composite outcome during the follow-up period, consisting of:

1. **≥7 % decrease in BMI** compared to post-hospitalization baseline BMI.

Rationale for 7 %: A 7% decrease in BMI reflects a significant deviation from expected weight gain in patients starting at a minimum BMI of 16, signaling potential relapse.

1. **Re-hospitalization for anorexia nervosa-related complications** (e.g., significant weight loss, medical instability). Data of hospitalization will be collected from hospital journal registers.
2. **Initiation of additional intensive psychiatric or nutritional interventions**, including day-patient or inpatient programs. Data of additional interventions will be collected from hospital journal registers.
3. **Self-reported significant deterioration in eating disorder symptoms** (e.g., severe food restriction, purging) as assessed by validated scales such as the Eating Disorder Examination Questionnaire 6.0 (EDE-Q 6.0).

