***Halt and/or Early Termination Criteria***

Halt and/or Early termination may be initiated if any of the following occurs:

- Unacceptable or unforeseen safety concerns, including unexpected serious adverse reactions (SUSARs) or a pattern of adverse events suggesting increased risk.
- Insufficient recruitment, defined as fewer than 30% of the planned number of participants being enrolled within 18 months of trial initiation.
- Emerging external evidence (e.g. from other clinical trials or meta-analyses) indicating that the investigational product poses a significant safety risk or is no longer ethically justifiable to study.
- Ethical concerns raised by the Safety Review Committee, monitor oversight or regulatory authorities.
- Withdrawal of essential approvals, resources, or study drug availability.

In the event of early termination or temporary halt, all relevant regulatory authorities (including CTIS, Läkemedelsverket, and EPN) will be notified within 15 calendar days, as per applicable regulations. The reason for halt and/or early termination will be documented and explained in the final report.

Safety Review committee and monitor clearance will be required before resuming after a temporary halt not leading to and early termination.

- End of the Clinical Trial: When the last participant completes the last follow-up visit at week 52.

6. Subject Selection

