10.2 Statistical Analyses

This will be an open label, two-arm, active comparator (TAU; treatment as usual), , randomized controlled, between- and within-subjects, design in up to 40 completing patients meeting DSM-5 criteria for eating disorders. The patients will be randomly allocated to the psilocybin treatment-arm. The study analyses will enable comparison of efficacy between psilocybin-treatment and treatment as usual, as well as longitudinal within-patient efficacies.

- Primary Baseline Analyses:
  The primary analyses will involve descriptive statistics for demographic and baseline characteristics, ensuring comparability across groups, and control for follow-up measurements.
- Primary Endpoints analysis
- We will analyse differences in the number of participants and severity experiencing AE/SAE between the groups standardized forms for AE/SAE capturing: Event description, Start and end dates, Severity (e.g., mild, moderate, severe), Relatedness to intervention (assessed by safety review committee), Action taken.

The primary statistical methods will be:

- Descriptive Frequencies and Percentages.
- Comparing Proportions (Most Common for "Incidence") (Chi-squared test (or Fisher's Exact Test): Fisher's exact test is preferred for small cell counts (<5).
- Risk Ratio (RR) or Odds Ratio (OR) with Confidence Intervals: Report these measures of effect size to quantify the magnitude and precision of the difference between groups. An RR > 1 would indicate a higher risk in the intervention group.
- Comparing Severity and Relatedness is assessed with Mann-Whitney U test or Student t-test to compare severity distributions between groups.
- Secondary Endpoints:
  For secondary endpoints (e.g., changes in fMRI connectivity, BDNF, rating scales), group comparisons, including t-test, ANOVA, and Repeated Measures ANOVA will be utilized. When controlling for variables such as individual differences, ANCOVA or MANCOVA will be utilized. Principal component analysis (PCA) or independent component analysis (ICA) may be applied to identify patterns in fMRI data. Task-based fMRI data will be analysed using univariate models to investigate treatment effects in syndrome-related neural circuits (Celeghin et al., 2023; Bronleigh et al., 2022). Endpoints include longitudinal between- and within-person analyses.

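### The primary SAE comparison pools admissions for anorexia nervosa, which are also relapse events, with all other SAEs, so a drug harm and a benefit on relapse can cancel

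*Protocol*

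**What the plan says.** Section 4.3 sets the primary endpoint as "Incidence of adverse events (AEs) and serious adverse events (SAEs) during the trial period". Section 9.1 defines an SAE to include anything that "at any dose requires inpatient hospitalization or prolongation of existing hospitalisation"; the cause of the admission plays no part.

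Section 4.4 lists "Re-hospitalization for anorexia nervosa-related complications" as a component of the relapse endpoint. A further component is the start of intensive psychiatric or nutritional care, "including day-patient or inpatient programs".

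Section 10.2 fixes the primary comparison: "We will analyse differences in the number of participants and severity experiencing AE/SAE between the groups". It uses a chi-squared or Fisher test and a risk ratio or odds ratio, read as follows: "An RR > 1 would indicate a higher risk in the intervention group". Relatedness is recorded and compared separately. Section 9.2 gives the causality judgement to the investigator and has a category for events that the underlying disease explains; 10.2 gives the judgement to the Safety Review Committee.

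Sections 8.2, 9.3 and 11.2 start AE/SAE collection at the first dosing. The TAU arm has none.

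**The concern.** One admission for anorexia nervosa enters the primary endpoint as harm and a secondary endpoint as lack of efficacy. The trial enrols patients who have already lost weight after restoration (6.1), follows them for 12 months, and aims to show less relapse. If that aim is met, the SAE ratio falls for a reason unrelated to toxicity, and an excess of drug-caused SAEs can disappear into a ratio near or below 1. The relapse result gives no warning, because it would look favourable. The primary safety answer is then partly the efficacy answer, and the protocol plans no comparison that pulls them apart.

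**Working it through.** **The plan's own figures.** There is nothing to reproduce. Section 10.4 states that no power calculation was made, and no SAE or admission rate is given. The relapse figure in Section 2 (can exceed 50% among those who recover) is not a 12-month admission rate, so it is not used as one.

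**Inputs from the protocol.** 20 per arm, 1:1 (5.1, 10.4); two-sided 0.05 (10.3); Fisher's exact test for small cells (10.2).

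**Assumptions.** TAU risk of an anorexia admission *a* = 10% to 50%. Ratio of that risk on psilocybin *r* = 1, 0.75 or 0.5. Drug-caused SAE risk on psilocybin *d* = 10%, 20% or 30%. Independent events, no other SAEs, and SAEs captured in both arms.

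**Formula.** Any-SAE risk on psilocybin = 1 − (1 − *d*)(1 − *a·r*); on TAU = *a*. The two are equal when *d* = *a*(1 − *r*)/(1 − *a·r*).

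**Drug-caused SAE risk that cancels exactly:**

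| TAU admission | admissions cut by 25% | admissions halved |
|---|---|---|
| 10% | 0.025/0.925 = 2.7% | 0.05/0.95 = 5.3% |
| 20% | 0.05/0.85 = 5.9% | 0.10/0.90 = 11.1% |
| 30% | 0.075/0.775 = 9.7% | 0.15/0.85 = 17.6% |
| 50% | 0.125/0.625 = 20.0% | 0.25/0.75 = 33.3% |

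**Worked case.** *a* = 30%, *r* = 0.5, *d* = 20%: 1 − 0.80 × 0.85 = 32% against 30%, a risk ratio of 1.07. Without anorexia admissions the same harm is 20% against 0%.

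**Dilution when psilocybin has no effect on admission.** *a* = 30%, *r* = 1, *d* = 20%: 1 − 0.80 × 0.70 = 44% against 30%, a risk ratio of 1.47. The excess stays visible but is diluted.

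**Exact power of the two-sided Fisher test to show an excess, TAU admission 30% where pooled:**

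| Drug-caused risk | anorexia admissions removed | pooled, no effect on admission | pooled, admissions halved |
|---|---|---|---|
| 10% | 4% | 4% | 0.3% |
| 20% | 37% | 9% | 2% |
| 30% | 76% | 18% | 6% |

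In counts, significance needs 5 against 0 without admissions, and 14 against 6 once six TAU patients have been admitted.

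**If TAU admissions are not captured as SAEs.** The bias turns round. With 30% admission in both arms and no drug-caused SAE at all, the expected count is 0.30 × 20 = 6 on psilocybin against 0 recorded on TAU, beyond the 5 against 0 needed for significance.

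**The case against.** Hospitalisation is an ordinary seriousness criterion, and under randomisation an all-cause SAE ratio is a legitimate net comparison that matches the stated endpoint. Section 10.2 speaks of higher risk in the intervention group, not of risk caused by the drug. That stands, and it is why the all-cause comparison should stay.

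Relatedness is rated, underlying disease is named as an alternative explanation, and relatedness is compared between groups. This helps in reading single cases. It does not give a between-arm separation: the rating is made unblinded, relatedness to psilocybin has no clear meaning for a TAU patient, and 9.2 and 10.2 name different assessors.

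An extra table by cause could be left to a statistical analysis plan. But the protocol itself fixes the endpoint, the test and how the ratio is to be read, so the pooling is its own choice.

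Power is poor anyway: about 4% for a 10% drug-caused risk even with anorexia admissions removed, and Section 5.1 concedes limited power. True, but pooling also moves the estimate, not only its precision.

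A reader might infer that the halt criterion in 5.4 counts disease events as toxicity. The text does not support this. It sets no SAE count. A SUSAR must be unexpected and suspected to be caused by treatment, so an admission judged unrelated does not qualify. What remains is a judgement on "a pattern of adverse events suggesting increased risk", where including these admissions would tend to raise a signal rather than hide one. Restricting that judgement to other SAEs would narrow a safety rule and could hide drug-induced worsening of the disease. The boundary is not clean either: 4.4 includes medical instability among anorexia-related complications, and the earlier psilocybin study in anorexia saw post-treatment hypoglycaemia, asymptomatic and resolved within 24 hours.

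**Conclusion.** The concern holds for the primary between-arm SAE comparison and no further. Admissions for anorexia nervosa sit in both the primary safety endpoint and the relapse endpoint, nothing separates them in the planned SAE comparison, and a fall in relapse admissions can offset a drug-caused excess.

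The size depends on rates that the protocol does not give. If admissions were halved, the cancelled drug-caused risk runs from about 5% at 10% TAU admission to about 33% at 50%; with a 25% reduction it runs from about 3% to 20%. Full cancellation needs a real reduction in admissions and equal SAE capture in both arms. A reader might also infer that anorexia admissions will dominate the SAE count; the protocol has no figure to show that. The overlap is not the trial's main limit for rare harms, since 20 per arm already is. This is a cheap improvement to how the primary result can be read, not an error in the SAE definition.

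**What to change.** - Leave 9.1 unchanged: every admission remains a reportable SAE.
- In 10.2, keep the all-cause SAE comparison and prespecify two more by arm: (a) SAEs excluding admissions for anorexia nervosa and (b) those admissions alone, read beside the relapse endpoint.
- Fix in advance how an admission is classified, including medical instability soon after dosing, and record the reason for each admission in both arms. Section 8.1 confirms hospitalisation from medical records but does not say that the reason is captured.
- Show the Safety Review Committee (9.5) all three counts by arm. Leave the halt criterion in 5.4 unchanged.
- Reconcile the collection start in 8.2, 9.3 and 11.2 with the TAU arm, so that both arms have the same capture window.

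The cost is some wording and one table. The small downside is that the cause of each admission is judged open-label; retaining the total covers this, because no event can leave the comparison through classification.

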9.2 Assessment of Adverse Events

-Events will be assessed by the clinical team for causality, intensity, and seriousness and potential relationship to treatment (psilocybin 25mg).

The investigator is responsible for determining whether there is a causal relationship between the AE/SAE and use of the investigational medicinal product.

Consideration should be given to whether there is a reasonable possibility of establishing a causal relationship between the adverse event and the investigational medicinal product based on the analysis of the available evidence.

All AE can be categorized as either likely related, possibly related, unlikely related or not related, in accordance with the definitions below:

Likely related: Clinical event, including abnormal results from laboratory analyses, occurring within a reasonable time after administration of the intervention/investigational medicinal product. It is unlikely that the event can be attributed to underlying disease or other medications but is most likely caused by the investigational medicinal product and its emergence is reasonable in relationship with use of the investigational medicinal product.

Possibly related: Clinical event, including abnormal results from laboratory analyses, occurring within a reasonable time after administration of the intervention/investigational medicinal product. The event could be explained by the investigational medicinal product and its emergence is reasonable in relationship with use of the investigational medicinal product, but there is insufficient information to determine the relationship. The event could be explained by an underlying disease or other medications.

Unlikely related: Clinical event, including abnormal responses from laboratory tests, unlikely to be related to the intervention/investigational medicinal product and can be reasonably explained by other medication or underlying disease.

Not related: Clinical event, including abnormal results from laboratory analyses, that is not reasonably related to the use of the intervention/investigational medicinal product.

Those AEs which are suspected of having a causal relationship to the investigational medicinal product will be followed up until the subject has recovered or is well taken care of and on the way to good recovery.

If the reporting investigator does not provide any information on causality, the sponsor should consult with the reporting investigator and encourage the expression of a position on this issue. The sponsor must take into account the assessment of causality provided by the investigator. If the sponsor disagrees with the investigator's assessment of causality, both the investigator's and the sponsor's views should be included in the report.

Each adverse event shall be classified by an investigator as mild, moderate or severe.

Mild: The adverse event is relatively tolerable and transient in its nature but does not affect the subject’s normal life.

Moderate: The adverse event causes deterioration of function but does not affect health. The event can be sufficiently unpleasant and interferes with normal activities but does not completely obstruct them.

Severe: The adverse event causes deterioration of function or work ability or poses a health risk to the subject.

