Currently, there are no approved pharmacological treatments for anorexia nervosa (Rahkonen et al., 2022). However, three pilot clinical trials have been approved and activated. NCT04052568 from John Hopkins is currently active. NCT04505189 from Imperial College is finished but not published. The third pilot study assessed the clinical tolerance and safety of 25mg psilocybin supported by psychological intervention in female AN patients with a BMI of 19 (Peck et al., 2023). The study found no significant changes in ECG, vital signs, or suicidality, and all adverse events (AEs) were mild and temporary. Two participants developed asymptomatic hypoglycemia post-treatment, which resolved within 24 hours with no other significant changes in laboratory values. Most participants reported subjectively meaningful experience, and a majority expressed that a second dose would have been beneficial. The study also observed significant reductions in eating disorder symptoms one-month post-treatment.

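### The adverse-event grades in section 9.2 overlap: every Moderate event also meets Severe, so the severity comparison under the primary endpoint analysis rests on grades that are not unique.

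*Protocol*

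**What the plan says.** Protocol section 9.2 requires one grade per event: "Each adverse event shall be classified by an investigator as mild, moderate or severe". The three definitions are:

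- The lowest grade reads "Mild: The adverse event is relatively tolerable and transient in its nature but does not affect the subject’s normal life", with no mention of risk to health.
- The middle grade begins "Moderate: The adverse event causes deterioration of function but does not affect health" and adds a second sentence, "The event can be sufficiently unpleasant and interferes with normal activities but does not completely obstruct them", the only place where complete obstruction is named.
- The top grade reads "Severe: The adverse event causes deterioration of function or work ability or poses a health risk to the subject", a list of alternatives of which any one is enough.

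The section gives no precedence rule, such as using the highest grade that applies.

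Section 4.3 defines the primary endpoint as "Incidence of adverse events (AEs) and serious adverse events (SAEs) during the trial period". Severity is not named there. It enters in section 10.2, under the primary endpoint analysis: "We will analyse differences in the number of participants and severity experiencing AE/SAE between the groups". That section names the three grades and plans a Mann-Whitney U test or a Student t-test on their distribution. Section 5.1 describes the trial as open-label.

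**The concern.** A three-level scale gives a reproducible result only if each event fits one level. Here the same condition, loss of function, appears in both Moderate and Severe. In Severe it is one of several alternatives joined by *or*, so it is enough by itself. Two investigators who follow the text faithfully can record different grades for the same event, and both are right.

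At stake is the severity comparison between arms in a trial whose primary objective is safety and tolerability. The choice between two valid grades is made by someone who knows the allocation. A statistical analysis plan cannot repair this later. Under section 9.3 events are logged by the clinicians at each contact, and the recorded grade does not show which definition was applied.

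**Working it through.** The protocol states no figure on this point, so there is none to reproduce. The check is of the logic of the definitions, followed by an illustration.

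**1. Coding the definitions (section 9.2).** Six yes/no attributes of an event: T tolerable, R transient, N affects normal life, F loss of function or work ability, H affects or endangers health, O completely obstructs normal activities.

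- Mild = T and R and not N
- Moderate = F and not H and N and not O
- Severe = F or H

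Combinations with F or O but without N are excluded as impossible. With N absent, F and O are absent too, and T, R and H are free: 2³ = 8. With N present, the other five are free: 2⁵ = 32. Total 8 + 32 = 40.

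**2. Which grades apply.**

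| Grades met | Combinations |
|---|---|
| Mild only | 1 |
| Mild and Severe | 1 |
| Moderate only | 0 |
| Moderate and Severe | 4 |
| Severe only | 23 |
| None | 11 |
| Total | 40 |

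- Moderate fixes F = 1, H = 0, N = 1, O = 0 and leaves T and R free: 2² = 4 combinations. All have F = 1, so all 4 meet Severe. Dropping the second sentence of Moderate does not alter this, because F is still required. If the highest applicable grade were used, Moderate would be empty.
- Mild fixes T = R = 1 and N = 0 and leaves H free: 2 combinations. The one with H = 1 also meets Severe. If such an event is not transient, it is Severe only.
- The 11 ungraded combinations include, for example, an event that is not transient but involves no loss of function and no health risk.

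**3. Effect on the planned comparison (assumed data).** The worst grade per participant is assumed as none/mild/moderate/severe = 4/8/7/1 on psilocybin and 8/8/3/1 on TAU, 20 per arm. *Literal* means that an event meeting Moderate is recorded as Severe.

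| Reading (psilocybin / TAU) | Severe, psilocybin v TAU | Fisher p | Mann-Whitney p |
|---|---|---|---|
| Moderate kept / kept | 1 v 1 | 1.00 | 0.126 |
| Literal / literal | 7 + 1 = 8 v 3 + 1 = 4 | 0.30 | 0.110 |
| Literal / kept | 8 v 1 | 0.020 | 0.054 |
| Kept / literal | 1 v 4 | 0.34 | 0.237 |

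The last two rows show what the text permits if the two arms are graded on different readings. They do not predict that this will happen. In every row the number of participants with any AE is 20 − 4 = 16 versus 20 − 8 = 12.

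**4. Check of the remedy.** Redefine Mild = T and R and not N and not H, leave Moderate as it is, and set Severe = O or H. The 40 combinations then split into Mild only 1, Moderate only 4, Severe only 28 and none 7 (1 + 4 + 28 + 7 = 40). No combination carries two grades.

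**The case against.** **The primary endpoint is untouched.** This stands. A reader might infer that the primary endpoint has no unique value. Section 4.3 defines it as AE and SAE incidence, which is the same under every reading, and seriousness has its own criteria in section 9.1. Only the severity tabulation and its test are affected.

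**The planned rank test barely moves.** In the example it goes from 0.126 to 0.110 when both arms switch together. That stands for a consistent switch. The count of participants with a severe event still changes from 1 v 1 to 8 v 4, and nothing in the text secures consistency between arms.

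**The intended boundary can be inferred.** Moderate is capped by no effect on health and by less than complete obstruction, so Severe was presumably meant to begin there. This is a sensible guess, but Severe contains no obstruction condition and says instead that loss of function is enough.

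**The Mild/Severe overlap is narrower than it looks.** A reader might infer that any symptom-free event with a health risk is both Mild and Severe. Mild also requires the event to be tolerable and transient, so a persistent one is Severe only.

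**The earlier anorexia study does not prove the overlap.** Of that study the background section reports "Two participants developed asymptomatic hypoglycemia post-treatment, which resolved within 24 hours" and calls all its adverse events mild. One might take this as the protocol grading such an event as Mild while section 9.2 would make it Severe. However, the protocol is summarising grades assigned under that study's own scheme, which is not shown. Whether such an event poses a health risk under section 9.2 is a clinical judgement that the protocol does not make.

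**Conclusion.** Wrong as written, and limited to the severity grades. On the literal text Moderate lies wholly inside Severe: all 4 combinations that meet Moderate also meet Severe, and none is Moderate only. One of the 2 combinations that meet Mild also meets Severe. No precedence rule resolves either overlap, and the grades are assigned by investigators who know the arm.

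The Moderate-within-Severe result rests only on the repeated loss-of-function condition. The other counts rest on the coding above, which treats an effect on health and a health risk as one attribute. The counts of 1 v 1 against 8 v 4 come from assumed data and show scale only. How many real events would fall in the overlap cannot be known from the protocol.

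**What to change.** Revise section 9.2 and the AE form before the first event is graded, so that the three grades exclude one another and the health-risk criterion is kept. For example:

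- **Severe:** replace the clause on loss of function or work ability with *completely obstructs normal activities*, the bound already used in Moderate. Keep the health-risk alternative.
- **Mild:** add *and poses no health risk*.
- **Moderate:** no change is needed for uniqueness. Use the same term for health in all three grades, so that an effect on health and a health risk are not read as different things.

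As shown above, this leaves no event with two grades. Seven combinations would still have none: 3 do not affect normal life but are not tolerable or not transient, and 4 affect normal life without loss of function, complete obstruction or health risk. One added sentence assigning these would make the scale complete.

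Dropping the health-risk criterion from Severe, so that the scale runs on activity alone, would also give unique grades but is not recommended. A symptom-free glucose or ECG finding that poses a risk but falls short of the seriousness criteria in section 9.1 would then be neither severe nor serious, although section 8.2 monitors both.

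The cost is wording only, with no added procedures or visits. Any event already graded under the current text would need regrading from its description.
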